## Abstract

Black girls are disproportionately impacted by HIV and STIs in the United States. Black male caregivers are underutilized in family-based HIV/STI prevention programming and offer a novel opportunity to protect Black girls. This study will evaluate the efficacy and implementation of an HIV/STI prevention program delivered to Black girls and male caregivers in community settings. IMAGE: IMARA for the Male Caregivers and Girls Empowerment was adapted from IMARA, an evidence-based mother-daughter intervention to decrease HIV/STI infection and increase communication and healthy relationships among girls and their male caregivers. Using an efficacy implementation design, we will test the effectiveness of IMAGE compared to a time-matched general health promotion program across six community-based organizations. Aim one will evaluate IMAGE in a 2-arm randomized controlled trial with 300 14-18-year-old Black girls and their male caregiver dyads in Chicago, IL. We hypothesize that girls who receive IMAGE will have lower STI incidence (*primary outcome),* fewer sexual partners, and more consistent condom use (*secondary outcomes*) at 6- and 12-months compared to girls in the health promotion program. Guided by the 3-Step Implementation Model, our second aim is to identify and describe factors (barriers, facilitators) and processes affecting implementation in community settings. HIV and STI disparities go beyond individual-level factors, and male caregivers may protect girls by being a sexual health resource. This study will facilitate rapid CBO uptake and ownership of IMAGE if effective.

**Trial Registration:** ClinicalTrials.gov NCT06266416

## Introduction

Sexually transmitted infections (STIs) have been increasing disproportionately among Black girls and women in the United States (US). Among females aged 15–24 years, STIs are highest among Black girls and women across all US regions [1]. Rates of chlamydia among Black girls are five times the rate of white girls [1], further amplifying their risk for poor sexual and reproductive health (SRH) outcomes (e.g., pelvic inflammatory disease, infertility, HIV)[2]. In Chicago, STI rates are highest among 13–29-year-old Black females, and in 2018, 56% of new HIV diagnoses were among Black women [3]. During the COVID-19 pandemic, treatment of STIs dropped as new barriers to reproductive health care exacerbated existing challenges. The pandemic also illuminated high rates of intimate partner violence, a well-known correlate of HIV/STI [4].

Elevated HIV/STIs are associated with sexual violence [5], and estimates predict that one in every four Black girls will rates be sexually abused before the age of 18 [5,6]. During the COVID-19 pandemic, sexual education, mental health, and SRH services and curricula were nearly abandoned [7,8], exacerbating barriers to care and burdening individuals and their families with SRH education. Familial protection and family-based interventions may prevent exposure to sexual violence and STIs among Black girls while simultaneously strengthening family relationships and girls’ SRH [9–12]. *Becoming a Sexual Black Woman* is a framework that describes the sexual vulnerability and resilience of Black cisgender women during three developmental phases (Girl, Grown, and Woman) [13]. It details how sociocultural conditions exacerbate risk at each phase and how familial protection may prevent Black girls’ exposure to sexual violence and STIs [12,14]. Interventions that strengthen family relationships and communication align well with this framework and have demonstrated success in reducing sexual risk and STIs among Black girls [15,16]. For example, IMARA (Informed Motivated, Aware, and Responsible about AIDS) an evidence-based intervention for Black girls and their female caregivers, revealed a 43% reduction in STIs one year after the program ended [10].

Most family-based intervention programs focus on female caregivers (i.e., mothers, aunts, and sisters) and their role in the SRH of Black girls and young women [10,17,18]. Yet, Black male caregivers (BMC), inclusive of fathers, uncles, grandfathers, brothers, etc., often neglected in family-focused interventions, have a unique role in educating and protecting Black girls as they navigate understandings of sex, sexual violence, body image, and other topics considered taboo to discuss in a girl-male caregiver relationship [19–22]. Male caregiver involvement specifically might offer distinctive protection against sexual violence exposure during girls’ sexual development [23]. Evidence suggests that SRH programs that include male caregivers have been associated with later sexual debut and increased condom use in Black girls [19,22,24], as well as improved communication, relationship quality, and less condomless sex in boys [25–27]. Black girls want SRH information from male caregivers [23], and men want to be involved in protecting girls [28]. Engaging BMC in interventions may empower Black girls to reject unhealthy sexual advances that often lead to sexual violence.

IMAGE was developed to address the needs of Black girls and their male caregivers using the *Becoming a Sexual Black Woman* theoretical framework and the Health Disparities Research Framework (HDRF) [29]. The *Becoming a Sexual Black Woman* framework emphasizes the impact of structural determinants of health (racism, discrimination, sexual violence, stereotyped messages, and adultification) on Black girls’ sexual development pathways, sexual health, and decision-making. HDRF describes the influence of structural factors at the individual, interpersonal, community, and societal levels relevant to understanding and reducing health disparities [29]. Consistent with the HDRF framework, *Becoming a Sexual Black Woman* highlights how lack of protection is a form of structural violence that Black girls experience at individual, interpersonal, and societal levels. IMAGE leverages BMCs desire to participate in girls’ lives and protect and support them while challenging toxic masculinity and the use of dominance, violence, and control to assert power and superiority.

We followed the ADAPT-ITT framework’s eight steps to systematically tailor and adapt the IMARA curriculum to create IMAGE [30]. We conducted in-depth interviews with 30 Black male caregivers and six focus groups with Black girls, male caregivers, and female caregivers, and these data-informed curriculum refinements. Adaptations also addressed drivers of structural violence for Black girls (i.e., stereotype messaging, lack of protection). Following the adaptations, we “theater tested” IMAGE with six girl-male caregiver dyads (n = 12) in collaboration with a community organization on the West side of Chicago. By delivering IMAGE at community-based organizations, we strengthen the relevance for Black communities and the likelihood the program will be adopted and sustained.

IMAGE was revised based on feedback from the theater testing and then pilot-tested with 20 girl-BMC dyads. Findings revealed strong feasibility and acceptability: 87% of those approached agreed to participate; 93% completed the full intervention; 94% rated IMAGE as acceptable; and fidelity of intervention delivery was 98% [31]. Retention at one-month follow-up was 100%, and 87% agreed to return at 6-months. Preliminary data showed promising improvements in behavior and theoretical mediators.

### Community-based implementation

We partnered with community-based organizations (CBOs) to build community ownership IMAGE. We tailored IMAGE’s implementation to facilitate ease of community uptake. Based on the Exploration, Preparation, Implementation, and Sustainability (EPIS) framework [32]. We simplified EPIS into 3-Steps that CBOs can use to implement evidence-based interventions [33]. This approach has been successful for other behavior change interventions in clinical and community settings [33–36]. The 3-step approach supports CBO implementation and future ownership.

## Methods

### Design

This is a 2-arm randomized efficacy and implementation trial of IMAGE for 14-18-year-old Black girls and their male caregivers. Girl and BMC dyads will be assigned to workshops randomized to IMAGE versus a time-matched health promotion program (FUEL). All participants will complete baseline, 6- and 12-month follow-up assessments via REDCap. Girls will provide urine to screen for three STIs (trichomoniasis, chlamydia, and gonorrhea). IMAGE engages male caregivers in HIV/STI prevention for girls, thereby increasing its relevance to Black communities and the likelihood of adoption and sustainability by CBOs. Therefore, we will also assess implementation outcomes at CBOs in Chicago.

#### Aim 1 (Efficacy).

We will assign 300 14-18-year-old Black girls and their male caregivers to workshops randomized to either IMAGE or FUEL and assess girls’ STI incidence, sexual partners, and condom use at baseline, 6- and 12-months. We hypothesize that girls who receive IMAGE will have lower STI incidence (primary outcome), fewer sexual partners, and more consistent condom use (secondary outcomes). We will explore associations of individual, interpersonal, and structural factors proposed by the B*ecoming a Sexual Black Woman* and HDRF framework on primary and secondary outcomes at all three time points (Fig 1).

**Fig 1 pone.0320164.g001:**
[figure not shown]
SPIRIT Schedule.

#### Aim 2 (Implementation).

We will identify and describe factors (barriers, facilitators, constraints) and implementation processes at six CBOs across Chicago.

#### Study setting.

We will deliver IMAGE at six CBOs on Chicago’s West and South sides impacted by structural factors (i.e., racism, poverty, crime, incarceration, and urban decay) implicated in high HIV and STI rates among Black communities. Neighborhoods in these areas are predominately Black, and Black females in these areas report the 4th highest rate of ever having sex (53%), the 3rd highest rate of sex before age 13, the 2nd highest rate of current sexual activity (40.6%) and have the highest rates of Chlamydia (1.921.0-2,688.4 per 100,000 people), and gonorrhea (973.7 - 1,536.2 per 100,000 people) [3]. Rates of sexual violence are also high in these neighborhoods [3]. The CBOs offer social services that address community resource needs and promote health and behavior change.

#### Aim 1 study population (efficacy).

Girls must be a) 14-18 years old; b) self-identify as African American, Black, or mixed race with African American or Black; c) speak English since measures are not normed for other languages; and d) identify an eligible male caregiver to participate in the study. BMC must be a) >  18 years old; b) self-identify as African American, Black, or mixed race with African American or Black; c) speak English since measures are not normed for other languages; d) be a current male caregiver to a Black girl 14-18 years old; and e) the girl’s legal guardian must agree to the male caregiver’s participation. BMC will be defined as men (fathers, grandfathers, uncles, brothers, cousins, etc.) who girls report playing a central role in their care and upbringing. Girls may or may not be sexually active, and information about girls’ sexual activity will not be shared with their male caregivers.

#### Recruitment, assent/consent, compensation and retention.

Recruitment will be multi-faceted. CBO will distribute flyers in the community and invite interested individuals to contact the IMAGE study. CBO will also contact eligible participants directly to inform them about the project and request permission for the research team to contact them. IMAGE staff will attend relevant community events to build relationships and conduct outreach. Using a screening and consent script, research staff will follow up with girls separately from guardians or male caregivers to conduct the screening, to obtain informed consent/assent with written, electronic signature via the e-consent module in REDCap, and to confirm the contact information of legal guardians and/or participating male caregivers. We will attempt to obtain girls’ assent/consent before we contact male caregivers, but participants may be screened in any order. Girls’ refusal to participate will precede consent or permission by male caregivers and legal guardians, regardless of the screening order. Dyads will complete surveys via REDCap at baseline, 6 and 12-month follow-up. Baseline survey assessments will occur before Day 1 of the intervention via REDCap. Girls and male caregivers will each receive $60 for completing the baseline assessment and an additional $65 for completing the entire workshop weekend. Participants are compensated $70 for the 6-month follow-up and $75 for the 12-month follow-up to recognize the value of retention over time. To overcome transportation barriers to STI treatment at the University of Illinois in Chicago Hospital Health Sciences System, we will provide an additional $5 in transportation compensation if needed. Participants’ transportation barriers will be assessed when scheduled for a workshop, and participant safety will be ensured. To maximize retention, we will use the strategies that were successful in our pilot (i.e., holiday cards and monthly phone calls or text messages) [31]. We will collect contact information for girls and male caregivers in multiple forms to find the most effective communication for each participant.

#### Randomization, sample size, and power.

We will use a stratified block randomization allocation to assign girl-BMC dyads to the treatment arm (IMAGE n = 150 or FUEL n = 150) prior to baseline assessment. Power analyses determined that a sample of 300 girls – 150 IMAGE and 150 FUEL is needed to assess efficacy on the primary outcome (STI incidence). Effect size (Cohen’s h) is a function of two proportions defined by Cohen; h = .2 is a small effect, h = .5 is a medium effect, and h = .8 is a large effect. We calculated the power to detect the effect of IMAGE vs. FUEL in reducing STI incidence as measured by having any of three STIs at 12 months post-intervention using a 2-sided test with alpha = .05. The new STI outcome at follow-up was a binary variable (yes/no to testing positive for at least 1 of the 3 STIs), because the study was not powered to examine specific STI outcomes. Based on the IMARA retention rate of 86% for Black female caregiver-girl dyads in Chicago [15], we evaluated the power of STI incidence (yes/no) at 80% retention over 12- months. Based on our previous work, we assume the STI incidence is 25% and 11% at 12 months for girls in the FUEL arm and IMAGE arm, respectively, which is a small-to-medium effect size of h = .37. With the proposed sample size, we will achieve 80% power to detect the intervention effect. We also calculated the standard effect size (Cohen’s d) for group mean comparisons with 80% power for our secondary continuous outcomes, where d = 0 is defined as no treatment effect. We can detect a small-to-medium effect size with the proposed sample size (d = .37).

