#### General statistical issues.

We will use Bonferroni correction to adjust for multiple comparisons as we will analyze multiple outcomes. We will control for Type I error in the analysis of the secondary outcomes but not the primary outcomes to capture important findings that may be obscured from the conservative limits imposed by Bonferroni correction. We will explore whether girls’ sexual behaviors are related to potentially important covariates (e.g., pubertal status) and use regression models to test their effects. To evaluate the impact of Black male caregivers on girls, we will include BMC’s characteristics as covariates in the regression model for girls’ outcomes. We will use a similar approach to evaluate the impact of girls on BMC over time. Missing data will most likely occur because of subject attrition. Based on our intervention studies, we expect 70%-85% retention in both arms. We will evaluate associations between dose (1 vs. 2 sessions) and efficacy. Missingness complicates statistical analyses via biased parameter estimates, reduced statistical power, and degraded confidence intervals. Based on our prior research, we expect minimal missingness in the data collection, but we will consider the item and unit nonresponse. An analysis using only completers is generally valid, assuming data are missing completely at random, but it is inefficient because it discards data points observed for non-completers. We will use all available data and produce valid inferences under the assumption that data are randomly missing. We will quantify the potential bias of these inferences should we suspect missing data to be non-random.

**Compare IMAGE vs. FUEL**^**TM**^

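### The stated 80% power assumes a 56% cut in STIs, while the only STI effect reported for the parent program is 43%, at which power is about 50-59%

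*Protocol article*

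**What the plan says.** The section on randomization, sample size and power plans two equal arms ("IMAGE n = 150 or FUEL n = 150") and tests the primary outcome, any of three STIs at 12 months, "using a 2-sided test with alpha = .05". Its rates are introduced with "Based on our previous work, we assume the STI incidence is 25% and 11% at 12 months", for FUEL and IMAGE in that order, "which is a small-to-medium effect size of h = .37". Retention is set at 80%, against 86% in the parent trial, and the section concludes that power is 80%.

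Three other statements bear on those inputs:

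- The Introduction says that the parent mother-daughter program, from which IMAGE was adapted, "revealed a 43% reduction in STIs one year after the program ended". The IMAGE pilot (20 dyads) is reported for feasibility, behavior and mediators, with no STI result.
- Under general statistical issues: "we expect 70%-85% retention in both arms".
- Under the Aim 1 study population: "Girls may or may not be sexually active". The assumed rates apply to all enrolled girls.

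**The concern.** A power statement is only as good as the effect it assumes. Here the assumed effect is credited to the team's earlier work, yet the one STI result from that work in the article is clearly smaller. The control condition also contains a brief HIV education module, and IMAGE itself has no reported STI data, so nothing in the article points to a larger effect than the parent program's.

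If the true effect were the size of the parent program's, the trial would have little better than an even chance of detecting it. A non-significant result could then be read as lack of efficacy by organizations deciding whether to keep offering IMAGE.

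Two lesser matters add to this. The power section uses one retention value, while the analysis section gives a range whose lower end falls short of what 80% power needs. And a 25% rate in a sample not selected for sexual activity needs a stated source population.

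**Working it through.** **Inputs.** Two-sided alpha 0.05, 150 per arm, rates of 25% and 11%, and 80% retention (power section); 70-85% retention (general statistical issues); 43% reduction (Introduction). Reading 43% as a relative risk reduction is my assumption.

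**Formulas**, with n analysed per arm:

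- Arcsine: h = 2·arcsin(√p1) − 2·arcsin(√p2); power = Φ(h·√(n/2) − 1.96).
- Pooled z: power = Φ((d − 1.96·SE0)/SE1), where d = p1 − p2, SE0 = √(2·p̄(1−p̄)/n) and SE1 = √((p1(1−p1) + p2(1−p2))/n).

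**Step 1: reproduce the plan's figure.** n = 150 × 0.80 = 120.

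- Arcsine: h = 0.371, matching the stated .37. Φ(0.371 × √60 − 1.96) = Φ(0.914) = 82.0%.
- Pooled: d = 0.14, SE0 = 0.0496, SE1 = 0.0488. Φ((0.14 − 0.0972)/0.0488) = Φ(0.877) = 81.0%.

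The calculation is sound on its own inputs.

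**Step 2: implied effect.** 1 − 0.11/0.25 = 56%. A 43% reduction from 25% gives 0.25 × 0.57 = 14.25%, with h = 0.273.

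**Step 3: power for both effects over the expected retention.**

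| Retention (n per arm) | 25% vs 11%, pooled / arcsine | 25% vs 14.25%, pooled / arcsine |
|---|---|---|
| 70% (105) | 75.6% / 76.7% | 50.0% / 50.7% |
| 80% (120) | 81.0% / 82.0% | 55.5% / 56.2% |
| 85% (127) | 83.1% / 84.1% | 57.9% / 58.5% |

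For scale, 80% power at 25% versus 14.25% needs 214 analysed per arm (pooled) against the planned 120. That is 214/0.80 = 268 enrolled per arm, or 214/0.70 = 306.

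**Step 4: retention needed for 80% power at 25% versus 11%.** The arcsine formula needs 114 per arm, and 114/150 = 76%. The pooled formula needs 118, and 118/150 = 79%.

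**Step 5: clustering.** The power section states no allowance for delivery in workshops of 6-8 dyads. Take workshops of m dyads at 80% retention, with design effect 1 + (0.8m − 1) × ICC. The ICC values are assumptions, since the article gives none. With m = 8 and the pooled formula:

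- ICC 0.02: design effect 1.108; power 76.8% for 11% and 51.3% for 14.25%.
- ICC 0.05: design effect 1.27; power 71.0% and 46.0%.

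**Step 6: lower control rates, illustrative only.** With a 43% reduction, 80% retention and the pooled formula, a 20% control rate gives about 45% power and 15% about 34%. The article contains no figure that selects either rate.

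**Step 7: if 43% were a reduction in odds.** Control odds are 0.25/0.75 = 0.333. Multiplied by 0.57 they give 0.19, a risk of 16.0%. Power is then about 37-41% at 70-80% retention.

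**The case against.** The strongest reply is that there is no arithmetic error: the 80% reproduces. The 43% is a one-line summary of a different program, for girls and female caregivers, with no statement of whether it is a risk, odds or adjusted reduction. The 25% and 11% are credited to earlier work, and a journal article may leave their justification to the full protocol. All of this is fair. It limits the point to an unexplained gap between two figures that the article itself prints, and it makes the relative-risk reading of 43% a declared assumption.

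Three stronger readings are tempting, and the article does not support them:

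- *That every planning input is more favourable than the article's own figures.* Not so for retention: 80% lies inside 70-85% and below the 86% cited. Only the lower part of the range hurts.
- *That the 40.6% rate of current sexual activity quoted for the study area shows 25% to be too high.* It is a community behavior rate, not an STI incidence, and it enters none of the power figures above. If all infections arose among girls active at that rate, 25% overall would mean 0.25/0.406 = 62% of them. But that takes the area rate for the enrolled sample and ignores girls who start having sex during follow-up.
- *That the area chlamydia and gonorrhea rates contradict 25%.* They are rates per 100,000 people and leave out trichomoniasis, so they are not comparable with urine testing of every enrolled girl for three infections.

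**Conclusion.** The point holds in a limited form. The power calculation is correct for its inputs, but the assumed 56% reduction exceeds the 43% reported for the parent program, without explanation. Replacing 56% by 43% at a 25% control rate takes power from 81-82% to 55-56% at 80% retention, and to 50-59% across 70-85%. Nearly all of that fall comes from the effect size. Retention alone, at its lower end, takes 25% versus 11% to 76-77%. All these figures are before any clustering by workshop, which lowers them further.

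The conclusion rests on reading 43% as a relative risk reduction and on keeping the control rate at 25%. The article gives no STI incidence that shows 25% to be wrong. What eligibility without regard to sexual activity supports is a request to state the source population, not a claim that the rate is too high.

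**What to change.** In the section on randomization, sample size and power:

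1. State that 80% power holds only for 25% versus 11%, with roughly 76-79% retention or better (depending on the formula) and no clustering.
2. Add power for a 43% reduction at 70%, 80% and 85% retention, over a stated ICC range.
3. Give the source of the 25% and 11%, and say whether they come from girls unselected for sexual activity. If a 56% effect is expected, give the reason.
4. Align the retention figure with the 70-85% in the analysis section.

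In the Aim 1 analysis, pre-specify adjustment for baseline sexual activity, which the baseline survey already collects, in the primary model. The plan now chooses confounders by observed baseline imbalance. The precision gained cannot be quantified from the article.

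I would not widen the endpoint to infection at either visit in order to recover power: it would change the 12-month outcome on which the trial was sized, and the trial is under way.

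The cost is a table and some wording, with no extra enrolment. The downside is that the stated power becomes less favourable.

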**on STI incidence and risky sexual behavior:** We will evaluate treatment effects separately at 6- months and 12 months. We will also combine data to evaluate an average effect across both time points and to analyze the change from 6- to 12 months. We will analyze binary outcomes using logistic and continuous outcomes using linear regression. At a single time point, we will test the effect of the binary indicator for IMAGE vs. FUEL on the outcome, adjusting for confounders and the outcome at baseline as additional independent variables. We will use mixed-effects regression models to analyze the outcome by combining both time points, and we will include a random intercept term to account for intra-subject correlation. We will test an average effect across time points and effects on patterns of change from 6- to 12 months by including an interaction term between treatment and time. We will use survival analysis to examine sexual initiation over the course of the study. We hypothesize that non-sexually experienced girls in IMAGE will, on average, initiate sex later than FUEL participants. We will estimate the Kaplan-Meier survival curves and conduct long-rank tests to compare the two survival curves. We will use Cox regression models and its extensions (e.g., Cox’s Proportional Hazard Model with Time-Dependent Covariates) to test for the effects of other covariates such as age or socioeconomic status.

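### The detectable effect d = .37 for the continuous secondary outcomes does not allow for both the planned Bonferroni correction and the expected attrition; with two tests and 80% retention it is about .40

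*Protocol article*

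**What the plan says.** The section on randomization, sample size and power states that "a sample of 300 girls – 150 IMAGE and 150 FUEL is needed" for the primary outcome, STI incidence, "using a 2-sided test with alpha = .05". For attrition it says "we evaluated the power of STI incidence (yes/no) at 80% retention over 12- months". The same paragraph then turns to group mean comparisons of the continuous secondary outcomes at 80% power: "We can detect a small-to-medium effect size with the proposed sample size", with d = .37. No alpha, retention or analysis set is attached to that last figure.

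The section on general statistical issues says "We will use Bonferroni correction to adjust for multiple comparisons as we will analyze multiple outcomes". It goes on to confine this control to the secondary outcomes and to exempt the primary outcome. The number of comparisons is not given. On attrition it says "we expect 70%-85% retention in both arms".

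The Aim 1 (Efficacy) section names two secondary outcomes, number of sexual partners and condom use. The data reduction section adds a composite risk score alongside individual indicators. The section comparing IMAGE with FUEL evaluates effects separately at 6 and at 12 months, adjusting for the baseline value of the outcome.

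**The concern.** A detectable effect is tied to the alpha at which the test will be run and to the number of participants expected to be analysed. The plan commits to a stricter alpha for the secondary outcomes and expects to lose 15% to 30% of girls. The d that can be detected with 80% power must reflect both. If it does not, the protocol promises more power than its own testing rule delivers, and a null secondary result would later be read against an overstated 80%.

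This is a question about a figure that the protocol states, not about detail that could be left to an analysis plan.

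**Working it through.** **Inputs**
- 150 girls per arm; two-sided alpha .05; 80% retention, so 150 × 0.80 = 120 per arm (sample size section; alpha and retention are stated there for STI incidence).
- 70% to 85% retention, so 105 to 127.5 per arm (general statistical issues).
- Bonferroni family of m tests. Two outcomes are named, so m is at least 2. Illustrations: m = 3 if the composite score is added; m = 4 if two outcomes are each tested at 6 and 12 months.

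**Formulas** (two-sample comparison of means, normal approximation, n per arm)
- Detectable d = (z[1 − α/2] + 0.8416) × √(2/n), with α = .05/m.
- Power at d = .37 is Φ(.37 × √(n/2) − z[1 − α/2]).

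**Reproducing the stated figure**
- n = 120, α = .05: (1.960 + 0.8416) × √(2/120) = 2.8016 × 0.1291 = .362. Power at .37 is 82%. Exactly 80% power at .37 needs 115 per arm. This is the closest match to the surrounding text.
- n = 150, α = .05/3: (2.394 + 0.8416) × √(2/150) = 3.2356 × 0.1155 = .374. This also rounds to .37, but assumes that no girl is lost.

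The first reading omits the correction and the second omits the attrition.

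**Applying both, at 120 per arm**

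| Tests | α | z | Detectable d | Power at d = .37 |
|---|---|---|---|---|
| 1 | .05 | 1.960 | .362 | 82% |
| 2 | .025 | 2.241 | .398 | 73% |
| 3 | .0167 | 2.394 | .418 | 68% |
| 4 | .0125 | 2.498 | .431 | 64% |

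A noncentral t calculation gives .363, .400, .420 and .434, with power within one percentage point of the table.

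**Across the protocol's own retention range, with two tests**
- 70% (105 per arm): 3.083 × √(2/105) = .425; power at .37 is 67%.
- 80% (120 per arm): .398; 73%.
- 85% (127.5 per arm): 3.083 × √(2/127.5) = .386; 76%.

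**What .37 would need with two tests:** n = 2 × 3.083² / .37² = 138.9, so 139 per arm. That is 139/150 = 93% retention, above the top of the stated range.

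**The case against.** Several counter-arguments deserve weight.

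- **The inputs behind d are not stated.** A reader might infer that .37 was calculated at alpha .05 with 240 girls. That is the likeliest reading, but the paragraph does not say so, and another combination reproduces the figure. What can be shown is only that the correction and the attrition are not both in it.
- **The planned model adjusts for the baseline outcome.** If the baseline and follow-up values correlate at ρ, the detectable d shrinks by about √(1 − ρ²). To bring .398 down to .37, √(1 − ρ²) = .37/.398 = .930, so ρ is about .37. For four tests, .37/.431 = .858, so ρ is about .51. Such values are possible, but the protocol states none and presents .37 as a group mean comparison. This stands as a limit on the claim, which holds for the unadjusted comparison.
- **The shift is small.** At .40 to .43 the effect is still below .5, the value the section calls medium for h, so the small-to-medium label survives. This stands too.
- **Condom use.** A reader might go further and say that condom use can be analysed only in sexually active girls, which would shrink the sample and break the randomised comparison, since the plan also says "We hypothesize that non-sexually experienced girls in IMAGE will, on average, initiate sex later than FUEL participants". The documents do not support this as a shown error. Girls need not be sexually active to enrol, but no section restricts the condom-use analysis to those who are. The data reduction section lists non-condom use as an indicator, which could be coded for every girl. The outcome is not said to be continuous, so d may not apply to it. The sexual activity rates in the study setting section describe neighbourhoods, not trial girls at 12 months. All that can be said is conditional: if only active girls were analysed, the detectable d would be larger still.

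**Conclusion.** The stated d = .37 at 80% power does not hold for an unadjusted comparison of means once the plan's Bonferroni correction and its expected attrition are both applied. The smallest family the document supports, two tests, gives a detectable d of about .40 at 80% retention, with about 73% power at .37. Four tests give about .43 and 64%. Nowhere in the 70% to 85% retention range does .37 reach 80% power with two or more tests.

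This rests on equal arms, a two-sided family-wise alpha of .05 and no credit for covariate adjustment. The family size is the document's minimum at two; three and four are illustrations.

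A reader might infer that the trial is too small or that its main test is compromised. Neither follows: the sample size was set on STI incidence, which is exempt from the correction. This is a modest error in one stated figure.

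**What to change.** - State which secondary outcomes and time points form the Bonferroni family, and how many tests that makes.
- Replace d = .37 by the value for that family at the assumed retention: about .40 for two tests or .43 for four at 80% retention. State the alpha and the number per arm beside it.
- If .37 is to be kept on the strength of the baseline adjustment, state the assumed correlation and its basis.

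The cost is a few sentences and a slightly less favourable detectable effect. No change to sample size, data collection or the primary analysis is needed.
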